# Personalized behavior change program for glaucoma patients with poor adherence: a pilot interventional cohort study with a pre-post design

**DOI:** 10.1186/s40814-018-0320-6

**Published:** 2018-07-23

**Keywords:** Glaucoma, Education, Counseling, Adherence, Motivational interviewing, Tailoring

## Abstract

**Background:**

About half of people with glaucoma do not adhere to their recommended medications. Interventions for other chronic conditions have successfully utilized reminder systems and motivational interviewing (MI)-based counseling. This study was designed to pilot a personalized intervention that leverages these strategies to assess their impact on medication adherence in glaucoma patients.

**Methods:**

Glaucoma patients taking ≥ 1 medication will be pre-screened by telephone survey for adherence to their medication(s). Those who self-report poor adherence will be enrolled in a 3-month monitoring period to measure medication adherence using electronic medication monitors. Participants who are non-adherent (take </=80% of their medication doses) over the 3-month run in phase will be eligible for the study. We plan to enroll 57 participants who are non-adherent to their medications. Participants’ adherence will then be continuously measured with electronic medication monitors, by self-report, and via pharmacy refill data over 2 years, during which two successively more resource-intensive components of an intervention aimed to improve medication adherence will be administered. The first component is a 3-month period of reminders (audio and/or visual) and text message or automated phone call if a dose of medication is not taken within a pre-specified time frame. The second component is a 6-month MI-based counseling program with a trained glaucoma counselor. This component uses the *eyeGuide*, a computer-based personalized behavior change program that enables para-professional staff to provide personalized education and counseling for glaucoma. The primary outcome is change in medication adherence. The secondary outcomes include changes in clinical outcomes (intraocular pressure, IOP, and IOP fluctuation) and psychosocial mediators of adherence (e.g., competence, energy for change and satisfaction). Participants will undergo semi-structured interviews at 12 months to give feedback about the counseling program in order to improve it.

**Discussion:**

This pilot study will provide insight into ways to deliver more personalized health care to non-adherent glaucoma patients in order to better support them in managing their chronic disease.

**Trial registration:**

Retrospectively registered with ClinicalTrials.gov (NCT03159247).

**Electronic supplementary material:**

The online version of this article (10.1186/s40814-018-0320-6) contains supplementary material, which is available to authorized users.

## Background

Despite evidence from randomized clinical trials that medication reduces vision loss from glaucoma [1, 2], it remains the second leading cause of blindness in the United States (US) [3]. One major contributor to this is that about one-half of glaucoma patients are essentially “untreated” because they do not adhere to their medications [4, 5]. Poor adherence and poor clinical outcomes disproportionately affect the most vulnerable members of US society, older people, and minorities [6, 7]. As life expectancy in the US continues to increase, the prevalence of glaucoma will also increase. As there is already a projected shortage of ophthalmologists in the workforce [8], we will need to re-think the current paradigm of how a single physician is responsible for medical decision making, surgical intervention, counseling and educating patients, and coordinating care in a complex medical system. Team-based care is becoming essential where a larger team of medical staff help support patients’ chronic disease self-management. There is a compelling need to develop and test technology-based solutions to improving the quality of care a medical team can provide to improve medication adherence and the outcomes of care for patients with glaucoma.

Poor adherence to effective medications is a critical barrier to achieving better outcomes in glaucoma patients. The World Health Organization stated that “increasing the effectiveness of adherence interventions may have a far greater impact on the health of the population than any improvement in specific medical treatments [9].” Once diagnosed with glaucoma, at least half of patients do not adhere to their glaucoma medication regimen [4, 5, 10], return for follow-up [6], or persist with their medications over the longer term [11]. Patients who are not adherent have more severe visual field loss [12–14], which leads to steep declines in health-related quality of life [15–18] and increased risk of falls and motor vehicle accidents [19].

Adherence to glaucoma medications is rarely addressed during the clinical encounter [20, 21] because education and counseling programs are not part of standard glaucoma care. Qualitative research has demonstrated that patients often have a poor understanding of glaucoma and its treatment [22–25]. In addition to knowledge gaps, patients have numerous concrete and psychological barriers to managing their glaucoma such as skepticism that glaucoma will cause vision loss in the future when it is asymptomatic, issues with side effects and medication cost, problems remembering to take medication, and difficulties properly instilling the medication [26–28]. Eye drop instillation is rarely taught during the clinic visit, and many patients cannot properly instill their drops [29, 13]. For example, among glaucoma patients with visual impairment, one-third of patients who thought they could correctly instill their eye drops did not get their eye drop into their eye when they were video-recorded [29].

Uniform, scripted approaches to improve adherence have been shown to be ineffective [30, 31]. However, complex, individualized counseling interventions, especially those based in motivational interviewing (MI), have been shown to improve adherence and health outcomes in many chronic diseases [30, 31]. MI is a style of counseling that engages patients by discussing priorities and obstacles to facilitate intrinsic motivation to change health behavior [32]. MI is a counseling style consistent with the theoretical framework of self-determination theory [33], which postulates that an individual must develop personally compelling reasons to motivate a change in behavior. Self-motivation depends on meeting three basic psychological needs: relatedness, autonomy, and competence. A collaborative discussion based in MI techniques allows these needs be met and creates “energy for change.” (Fig. 1). Relatedness is promoted by expressing empathy during counseling. Autonomy is supported when the counselor helps the person overcome ambivalence and identify his own values and goals for managing disease. MI supports competence and self-efficacy by equipping the person with the knowledge and skills to work through barriers and implement routines to maintain the behavior change (create an “action plan”). MI and SDT will serve as the health communications framework for the tailored strategies for our interventions in the non-adherent glaucoma patient population. Few complex interventions based on these successful principles have been rigorously tested and none have been implemented into glaucoma care.

**Fig. 1 Fig1:**
[figure not shown]
Self-determination theory based theoretical model

The eyeGuide is a web-based, personally tailored, behavior change program based on MI principles and self-determination theory, developed from a systematic review of the glaucoma adherence literature [34], data from focus groups [35] and surveys [26], and iterative beta-testing with glaucoma patients [36] (Fig. 2). The eyeGuide was developed with user centered design; we tested the eyeGuide with patients and providers and when more than one person suggested something should be changed, we changed it. We continued this process until we no longer received substantive comments from patients and providers, which occurred after testing with 40 patients and 8 providers through three major design changes. The eyeGuide has two components woven together into a single web-based tool: an electronic health (eHealth) component and a semi-structured, tailored interview guide to facilitate an MI-based conversation. The eHealth component provides individually tailored disease and treatment information, and information on how other patients overcame similar barriers to optimize their disease self-management. Such technology-based eHealth innovations have great potential to extend the reach of physicians by enabling team-based care.

**Fig. 2 Fig2:**
[figure not shown]
eyeGuide tool screenshots

In this pre-post design pilot study, we will test the initial impact of two sequentially more resource-intensive components of a personalized eHealth intervention on medication adherence among non-adherent glaucoma patients: (1) real-time automated adherence reminders and (2) the eyeGuide MI-based counseling program. We will also explore the preliminary effects of these interventions on secondary outcomes including psychosocial mediators of adherence (e.g., competence, energy for change, satisfaction) and clinical parameters (intraocular pressure (IOP) and IOP fluctuation).

## Methods/design

In order to test the preliminary impact of the personalized eHealth intervention among non-adherent glaucoma patients, we will electronically monitor medication adherence longitudinally over 2 years. The two main components to be evaluated are (1) real-time automated adherence reminders using commercially available AdhereTech electronic medication monitors (AdhereTech, New York, USA) and (2) in-person tailored counseling with a medical assistant trained in MI (the eyeGuide program). Adherence will be monitored for all patients for a total of 2 years. Adherence will first be monitored for a 3-month period prior to the intervention to obtain baseline adherence and mitigate issues with regression to the mean and the Hawthorne effect [37]. Adherence will then be measured over a nine-month period of time during which the two interventions will be sequentially administered. Finally, adherence will be measured for 1 year after the conclusion of intervention to assess how well change in adherence is maintained over time.

### Ethics, consent, and permissions

Approval for the study was obtained from the University of Michigan Institutional Review Board (HUM00112614). Eligible participants will be assessed for willingness to participate in the study. Informed consent will be obtained at the first study visit for study participation alongside permission to access health information from the medical record and pharmacy refill data from participants’ pharmacies.

### Participants

Participants who have been seen at the University of Michigan Kellogg Eye Center, have a diagnosis of glaucoma (including glaucoma suspect and ocular hypertension), are aged ≥ 40, take ≥ 1 glaucoma medication, and speak English will be eligible to participate in the study. Eligible glaucoma patients will be sent a letter explaining the study along with an option to opt out of recruitment. Those who do not opt out will be called and their adherence status will be assessed by two survey methods of self-report to increase the probability of recruiting truly non-adherent patients (see Additional file 1 for measures to assess self-reported medication adherence). We will exclude patients who do not administer their own eye drops or who have a diagnosis of cognitive impairment or severe mental illness.

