An adherent event is defined as taking medication within a specified time window of a dose on the previous day. For a once daily medication, an adherent event is defined as taking the medication within 24 ± 4 h of the previous day’s dose. For a twice daily medication, an adherent event is defined as taking the first medication dose within 24 ± 2 h of the previous day’s first dose and taking the second medication dose within 24 ± 2 h of the previous day’s second dose. For a three times daily medication, an adherent event is defined as taking the medication dose (first, second, or third) within 24 ± 1.3 h of the previous day’s corresponding medication dose (first, second, or third). For a four-time daily medication, an adherent event is defined as taking the medication dose (first, second, third, or fourth) within 24 ± 1 h of the previous day’s corresponding medication dose. The biological efficacy of medications dosed multiple times daily declines when not taken on time [38–40]. However, when calculating adherence for medications dosed more than once a day, we compare the current day’s doses to the previous day’s corresponding doses rather than simply the previous dose (second versus first, or third versus second) as lifestyle and sleeping patterns can result in medication times that are not equally spaced. This method of calculating adherence also allows for large shifts (time zone changes for work or vacation) or gradual changes in times when medications are taken without overly penalizing the patient, which can happen when calculating adherence relative to a median time. Additionally, this method of measuring adherence ensures that adherence credit is not given for instances where bottles are opened numerous times just prior to a clinic visit [119]. For participants on more than one medication, adherence will first be measured at the medication level and then aggregated to the person level by dividing the total number of doses of all medication(s) taken on time by the total number of doses of all medication(s) prescribed. Baseline adherence will be calculated monthly during the 3-month monitoring period. The median monthly adherence will be designated as the baseline adherence score; choosing the median will help to mitigate the effects of regression to the mean. We will exclude patients from participating in the study whose median baseline adherence score is > 80% on all of their glaucoma medications after a baseline observation period of 3 months.

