### Outcomes

#### Primary outcome

The primary outcome is change in medication adherence (continuous variable for percentage of medication doses taken on time) measured by electronic medication monitors after each intervention. We will also measure adherence by three additional techniques in order to reflect different aspects of adherence behavior [51] and compare the techniques to one another: (a) video-recorded drop instillation, (b) self-reported adherence [52–55], and (c) pharmacy refill data. To assess how well patients can properly instill their eye drops, we will video-record patients instilling their eye drops during their third and fifth study visits, before and at the end of the eyeGuide intervention, respectively. Two masked assessors will review the videos and assess each participant for the following three techniques: (1) does the participant dispense a single drop, (2) does the drop get into the eye, and (3) does the participant touch the dropper tip to the ocular adnexa or extraocular structures. Self-reported adherence will be assessed with the Morisky questionnaire [56] (eight items, Cronbach *α* = 0.83), the Adherence to Refills and Medications Scale [57] (ARMS, 12 items, *α* = 0.81), and three additional questions about adherence from the glaucoma literature [55, 51]. These adherence questionnaires will be given at the baseline, 3-, 6-, 12-, and 24-month study visits.

Pharmacy refill data will be obtained by calling each participant’s pharmacy every 3 months to identify whether each prescribed medication has been filled. The medication possession ratio (MPR) is the proportion of days during a fixed time period where the patient had an adequate supply of medication to use at the prescribed frequency. MPR will be calculated at the patient level after combining refill data from all medications during a defined time period, as follows:$$ \frac{\mathrm{MPR}=\kern0.5em \#\mathrm{days}\ \mathrm{correct}\ \mathrm{amount}\ \mathrm{of}\ \mathrm{medication}\ 1+\dots +\#\mathrm{days}\ \mathrm{correct}\ \mathrm{amount}\ \mathrm{of}\ \mathrm{medication}\ 4}{\#\mathrm{elapsed}\ \mathrm{days}\ \mathrm{medication}\ 1+\dots +\#\mathrm{elapsed}\ \mathrm{days}\ \mathrm{medication}\ 4} $$

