Secondary outcomes include comparing adherence measured by pharmacy refill data, self-report, and successful eye-drop instillation to electronic monitoring using Pearson’s correlations. Changes in glaucoma skills and energy for change will be assessed after each intervention component and at 1 and 2 years post-intervention and compared with paired *t* tests and McNemar’s tests for continuous and categorical measures. All analyses will be conducted with SAS software, version 9.4 (SAS Institute, Cary, NC, USA).

The semi-structured interviews will be recorded and transcribed verbatim. Two investigators will read the transcripts and identify major themes. The data will be interpreted qualitatively using grounded theory [86]. A code book will be generated defining codes for each theme. Two investigators will then code the transcripts. Any areas of disagreement will be discussed until consensus is reached or adjudicated by a third researcher [87]. The coded content will be tallied to weight the frequency of the themes. The transcripts will also be analyzed by participant group, those who did and those who did not improve from the intervention. Themes from these two groups will be compared in a joint display to try to identify reasons why the program was not successful among some participants to identify areas for programmatic improvement.

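### Self-report and the monitor are both entry filters and are then correlated with each other, so the entry-period comparison in enrolled patients is truncated on both measures

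*Protocol article*

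**What the plan says.** The Protocol article sets two entry filters in sequence.

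- **Self-report.** Under Participants, patients are telephoned and "their adherence status will be assessed by two survey methods of self-report to increase the probability of recruiting truly non-adherent patients". The Abstract (Methods) adds: "Those who self-report poor adherence will be enrolled in a 3-month monitoring period". The scoring rules are in Additional file 1, which is not shown.
- **Monitor.** The Abstract says: "Participants who are non-adherent (take </=80% of their medication doses) over the 3-month run in phase will be eligible for the study". Baseline eligibility assessment excludes those "whose median baseline adherence score is > 80% on all of their glaucoma medications" after the 3 months.

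The same two measures are then set against each other. Primary outcome says the further adherence measures are taken "in order to reflect different aspects of adherence behavior [51] and compare the techniques to one another". Data analysis lists as a secondary outcome "comparing adherence measured by pharmacy refill data, self-report, and successful eye-drop instillation to electronic monitoring using" Pearson correlations. The self-report questionnaires are given at 0, 3, 6, 12 and 24 months. The limitations named in the Discussion are the missing control arm and the Hawthorne effect; selection on the two compared measures is not mentioned.

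**The concern.** Two measures are compared in people chosen by their values on both. Patients who do poorly on the monitor but report good adherence are the over-reporters, and none of them is ever monitored. Patients who report poor adherence but score above 80% leave at month 3. The enrolled sample starts in a single cell of the two-by-two table.

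Two misreadings could follow, in opposite directions. A low correlation could be taken to show that self-report tracks the monitor badly, when part of it is restriction of range. A low share of over-reporters could be taken to show that patients report honestly, when those who would not admit poor adherence were screened out by telephone.

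**Working it through.** **The plan's own figure.** The article gives no figure for this comparison. Its sample size for the primary paired test reproduces: SD of the difference = 0.20 × √(2 × (1 − 0.3)) = 0.2366, difference 0.10, two-sided 5%. The noncentral t gives n = 46 (power 80.1%), and 46/0.8 = 57.5 against the stated 57. Nothing below touches it.

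**Step 1. Who is left.**

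| | Monitor 80% or less | Monitor above 80% |
|---|---|---|
| Reports poor adherence | enrolled | monitored 3 months, then excluded |
| Reports good adherence | never monitored | never monitored |

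This follows from the two filters whatever the cut-offs in Additional file 1 are.

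**Step 2. Model for size (assumptions, not document figures).** Monitor score, telephone self-report and visit-1 questionnaire are trivariate normal. Both cuts are at the median; the Background's statement that about half of patients do not adhere supports this for the monitor, while the self-report cut is assumed. The telephone-monitor correlation ρ is 0.3, 0.5 or 0.7. Three variants, 4 million draws each:

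- A: the questionnaire relates to the monitor only through the telephone report, with retest correlation 0.8, so its unselected correlation is 0.8ρ.
- B: the questionnaire is as valid as the telephone report (correlation ρ), retest 0.8.
- C: as B, retest 0.5.

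**Step 3. Correlation of visit-1 questionnaire with monitor** (for ρ = 0.3 / 0.5 / 0.7).

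| | Unselected | Monitor cap only | Both filters (enrolled) | All run-in completers |
|---|---|---|---|---|
| A | 0.24 / 0.40 / 0.56 | 0.15 / 0.26 / 0.38 | 0.09 / 0.17 / 0.30 | 0.12 / 0.21 / 0.32 |
| B | 0.30 / 0.50 / 0.70 | 0.19 / 0.33 / 0.51 | 0.14 / 0.27 / 0.46 | 0.20 / 0.35 / 0.54 |
| C | 0.30 / 0.50 / 0.70 | 0.19 / 0.33 / 0.51 | 0.16 / 0.30 / 0.52 | 0.23 / 0.41 / 0.63 |

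The last column has a closed form. With r the unselected correlation and t the retest correlation, it is (r − 2ρt/π) / √[(1 − 2ρ²/π)(1 − 2t²/π)]. For C at ρ = 0.5: (0.5 − 0.1592)/(1 − 0.1592) = 0.3408/0.8408 = 0.41.

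**Step 4. Over-reporting: share of monitor-non-adherent patients reporting good adherence at visit 1.** Unselected, this is 1/2 − arcsin(r)/π.

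| | Unselected | Enrolled |
|---|---|---|
| A | 42% / 37% / 31% | 19% / 18% / 18% |
| B | 40% / 33% / 25% | 17% / 15% / 14% |
| C | 40% / 33% / 25% | 28% / 25% / 22% |

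**Step 5. Later visits.** A separate run used a fresh occasion for both measures, within-method retest 0.3 or 0.6, and 25% or 50% reporting poor adherence. Correlations return close to their unselected values: 0.27–0.30 for 0.3, 0.46–0.49 for 0.5, 0.65–0.69 for 0.7. Over-reporting is 15% to 54%, against 25% to 67% without selection.

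**Step 6. A figure the design does support.** The share of self-reported poor adherers whom the monitor confirms is 1/2 + arcsin(ρ)/π at median cuts: 60%, 67% and 75% for ρ = 0.3, 0.5 and 0.7. It moves with accuracy. In variant A the enrolled over-reporting share barely moves (19%, 18%, 18%).

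**The case against.** Several objections carry weight.

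- **A reader might infer that the comparison cannot show over-reporting at all.** The documents do not support that. The filters act only at entry, questionnaires run to month 24, reports may improve when doses do not, and a patient can admit missed doses yet overstate the level. The simulated shares in enrolled patients are well above zero.
- **A reader might infer that selection flatters self-report.** For the planned statistic it does the reverse: truncation lowers a Pearson correlation. That statistic is also blind to a systematic shift, with or without selection.
- **A reader might infer that the plan discards the excluded patients' data.** No section says so. Data analysis names no analysis set for this comparison, and the full protocol or analysis plan may already include all run-in completers. The point is therefore conditional on the comparison being run on enrolled patients.
- **The extra loss from the telephone screen is assumption-bound.** This stands. In variant C it adds almost nothing beyond the monitor cap (0.16, 0.30, 0.52 against 0.19, 0.33, 0.51).
- **Materiality.** This is a secondary comparison in a pilot, the screen has a sound recruiting purpose, and the article does not claim that self-report can replace the monitor. That limits the weight of the point, but the article states no limit on the comparison either.

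**Conclusion.** The point holds as a limit on the entry-period comparison. Run on enrolled patients, the months 0 and 3 comparison of self-report with the monitor is truncated on both measures. The Pearson correlation is attenuated: in the runs for visit 1 it loses roughly a quarter to two thirds of its unselected value (0.70 to 0.52 at the mild end, 0.24 to 0.09 at the severe end). Over-reporting is understated: about 14% to 28% in enrolled patients, against 25% to 42% without selection. Results describe only patients who admit poor adherence. The effect may weaken at later visits, where the simulated correlations largely recover, but no screened-out over-reporter is ever added to the sample.

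The direction follows from the two filters. The sizes rest on normal scores, median cuts and assumed correlations; the actual self-report cut-offs are not shown.

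**What to change.** 1. Run the baseline self-report versus monitor comparison on everyone who completes the run-in, including those excluded above 80%. Do the same at month 3 where the questionnaire was completed. Consent, the visit-1 survey and 3 months of monitor data already exist for these people. This removes truncation on the monitor and raises the correlation toward its unselected value in every variant above, though only modestly in variant A.
2. Report the share of self-reported poor adherers whom the monitor confirms at 80% or less, with its denominator. If that share were 60% to 75%, enrolling 57 would imply about 57/0.60 = 95 to 57/0.75 = 76 run-in completers, so 19 to 38 people beyond those enrolled.
3. Report the correlations by visit.
4. State under Primary outcome and Data analysis that truncation on self-report remains, because patients who report good adherence are not monitored, so over-reporting in glaucoma patients generally cannot be estimated.

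The cost is a little more analysis and a narrower claim about self-report. No new data collection is needed, and the primary outcome and sample size do not change.
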